### Recruitment process

The recruitment process for the trial began in September 2017. All eligible PHC located in Barcelona city, the central area of Catalonia (Bagés, Berguedá, and Solsonés) and the southern area (Baix Llobregat Nord) have been contacted and encouraged to participate in the study. The PHC who express interest receive a team presentation, explanatory dossiers, and informed consent papers. Those who wish to take part are required to consecutively recruit 16–24 patients who, after meeting inclusion criteria and signing the informed consent, will be randomized into two equally sized groups (IG and CG).

Different groups of healthcare workers will be involved in the field work:Recruiters: the patient’s assigned doctor and/or nurse.Nurses leading the psycho-educational groups, two per PHC.Evaluators blinded to the groups who carry out interviews at baseline, and at 3 months, and 12 months post-intervention.An external researcher in charge of patient randomization which is performed once all the necessary number of patients have signed the consent forms. The data gathering phases are explained in the work plan section.

All outcome variables will be assessed three times: prior to study commencement (baseline), after 3 months, and at 12 months after inclusion in the individual data collection sessions. Information about data collection and intervention programme timeline are detailed in the Table 2.

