**Secondary measurements:**

Improvement in control of chronic diseases (blood test and physical parameters), drug compliance (Morinsky-Green test and number of containers returned), quality of life (EQ-5D), medical service utilization (appointments and hospital admissions due to complications), and feasibility of the intervention (satisfaction and compliance). Evaluations will be blinded, and conducted at baseline, post-intervention, and 12 months follow-up.

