## Methods/design

### Study design

A randomized, multi-center, clinical trial composed of two groups with blinded response variables and a one-year follow-up. A cost-effectiveness study will also be performed. When each primary healthcare center (PHC) has a sample of 24 patients these are randomly allocated to either an intervention group (IG) or a control (CG). Data will be collected at baseline, and at 3 and 12 months post-intervention.

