### Intervention

#### Description of the psychoeducation group intervention

In order to homogenize the interventions, the research group has developed a protocol of 12 weekly sessions lasting 90 min led by two primary care nurses. Each group is made up of 8–12 participants [26]. The sessions will be held on PHC premises which have the necessary space and equipment.

The objectives of the 12 sessions are depicted in Table 1. The program provides: 1) health education about chronic pathology and depressive symptoms; 2) information on the relationship between depressive symptoms and chronic pathology; 3) health education regarding: diet, physical exercise, sleep, pleasant activities, social skills, pharmacological treatment, and adherence to treatment; 4) breathing techniques; 5) problem solving, behavioral activation, and cognitive-behavioral perspective on depression; and 6) self-esteem and assertiveness [26].

**Table 1 Tab1:** Content of the psychoeducational group program

lSessions	Objectives
1	• First contact with the group • Identification of depressive symptoms • Information on chronic pathology versus chronicity • Information on the relationship between depressive symptoms and chronic pathology • Breathing techniques
2	• Behavioural Activation I: Concern and problems.
3	• Behavioural Activation II: Concern and problems.
4	• How to take care to advance I ➢ Healthy diet ➢ Motivation for change (resources and difficulties)
5	• How to take care to advance II ➢ Physical exercise ➢ Pleasant activities, social skills
6	• How to take care to advance III ➢ Sleep ➢ Therapeutic compliance
7	• Problem solving I
8	• Problem solving II
9	• Self-esteem and assertiveness
10	• Cognitive-behavioural perspective I
11	• Cognitive-behavioural perspective II
12	• Group farewell • Final evaluation

To enhance the active role of the patient, each session is accompanied with homework. The participants are free to continue under pharmacological treatment.

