### Statistical analysis

The analysis is performed on an intention-to-treat basis. All the patients who have signed the informed consent and attended the initial interview are included. Missing data from the BDI-II evaluation during follow-up will be substituted by the last registered value (Last Observation Carried Forward strategy). At the beginning of the study descriptive statistics will be performed to evaluate the homogeneity between the two groups (IG and CG) with respect to demographic, clinical, and service utilization variables. In order to measure the main objective (rate of remission and response) logistic regression is employed in which the dependent variable is dichotomous (rate of remission and response). The patient’s group is the independent variable. Raw and adjusted odds ratio (OR) are calculated according to age, sex, pharmacologic treatment, and comorbidity. Repeated measure ANOVA analysis will be performed to determine the evolution of the dependent variables during follow-up. For the secondary resulting variables, control of the physical pathologies will be measured by logistic regression in which the dependent variable is dichotomous (control yes/no). The models will be adjusted in the same way as the principal one. Variable differences in the BDI-II rating and other scores with respect to baseline will be calculated. Student’s t test will be employed for the comparison between the groups’ variables and standardized effect size (SES; Kazis et al.1989) [44].

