The economic analysis will be carried out with a cost-effectiveness analysis to compare the expenses incurred from the psychoeducation intervention with those from habitual clinical practice over 1 year. The QALYs (quality-adjusted life years) obtained from the EuroQol questionnaire will provide the variable of effectiveness. That of cost will be obtained by measuring all the direct expenses generated by the participants from both groups and including any other related information. For instance, primary care consultations, referrals to specialists, hospitalization, additional tests, analytical tests, and medication expenses. The ratios and incremental costs for the IG versus CG will be calculated. Prices will be based on those of 2016 as the Oblikue database is the most complete for that period. As the healthcare costs will be generated over various years a constant discount rate of 3% per year will be applied. Finally, for the items with the greatest presence in the overall cost, a deterministic sensitivity analysis will be carried out to ensure robustness and reliability of the results obtained [45].

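### Follow-up visits are counted from two different starting points, so the timing of the primary outcome is not fixed and the 3-month BDI-II can precede the end of the course

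*Protocol article*

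**What the plan says.** **Visit times**
- Study design: "Data will be collected at baseline, and at 3 and 12 months post-intervention".
- Recruitment process, evaluator item: blinded evaluators "carry out interviews at baseline, and at 3 months, and 12 months post-intervention". In Measures, Table 3 sets its 3- and 12-month columns under a post-intervention heading.
- Recruitment process, next paragraph: every outcome variable is assessed before the study starts, then "after 3 months, and at 12 months after inclusion in the individual data collection sessions".
- Abstract, Secondary measurements: evaluations are "conducted at baseline, post-intervention, and 12 months follow-up".
- Measures, primary outcomes: remission and response are assessed in the short term and at one year, with no day zero.

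**Start of the course**
- Study design: "When each primary healthcare center (PHC) has a sample of 24 patients these are randomly allocated". Recruitment process asks each centre to recruit 16–24 patients consecutively, and an external researcher randomises them after the required number have consented.
- Description of the psychoeducation group intervention: the course is "12 weekly sessions lasting 90 min led by two primary care nurses".

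**Analysis**
- Statistical analysis, intention-to-treat set: "All the patients who have signed the informed consent and attended the initial interview are included".
- Statistical analysis, economic part: the cost of the intervention is compared "with those from habitual clinical practice over 1 year".

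Recruitment process refers to Table 2 for the timeline. That table is a figure that is not reproduced in the text at hand.

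**The concern.** The visit schedule fixes when the primary outcome is measured, and here two sections, and two adjacent paragraphs of one section, disagree. The design makes this more than a matter of wording. Inclusion happens patient by patient, while randomisation and session 1 happen centre by centre, after the quota is reached. The interval from inclusion to session 1 can therefore differ for every patient, and no upper limit on it is given.

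Each starting point brings its own problem:
- **Counted from inclusion**, an early recruit could have the short-term BDI-II part-way through the course, or before it. That would pull the short-term remission and response rates of the two arms together.
- **Counted from the intervention**, the last visit falls well after one year, while the QALY and cost comparison covers one year. Control patients attend no course, so nothing states from which date their visits are counted.

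The analysis set has a related fault. It is defined by consent and the initial interview. Consent precedes randomisation by design, and the interview can. As worded, the set can include a patient whose centre never reached its quota and who has no allocated arm.

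**Working it through.** The article gives no computed figure for visit timing, so there is none to reproduce. The sample size is not at issue here.

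**1. Slack between the 3-month visit and the last session**
- Twelve weekly sessions: session 1 to session 12 spans 11 × 7 = 77 days.
- Three months: 3 × 365.25/12 = 91.3 days.
- Slack: 91.3 − 77 = 14.3 days.

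On the inclusion count, the 3-month visit falls before session 12 whenever session 1 is more than about 14 days after inclusion.

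**2. Sessions held by the 3-month visit, inclusion count**

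The wait from inclusion to session 1 is not stated, so it is an assumption shown as a range. For a wait of w weeks, sessions held = the whole part of (91.3 − 7w)/7, plus 1, capped at 12, and 0 if 7w exceeds 91.3.

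| Wait (weeks) | Sessions held | Visit relative to session 12 |
|---|---|---|
| 0 | 12 of 12 | 14 days after |
| 2 | 12 of 12 | about the same day |
| 4 | 10 of 12 | 14 days before |
| 8 | 6 of 12 | 42 days before |
| 12 | 2 of 12 | 70 days before |
| 16 | 0 of 12 | 98 days before |

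**3. Share of a centre's patients affected, inclusion count**

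Assume N = 16, 20 or 24 patients are included evenly over F weeks and session 1 follows as soon as the centre is full. Patient i then waits F × (N − i)/(N − 1) weeks. The share waiting more than 14.3 days is:
- F = 2 weeks: 0%
- F = 4 weeks: 50%
- F = 8 weeks: 75%
- F = 12 weeks: 80–83%

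**4. Visits counted from the end of the course**

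Months from inclusion = (7w + 77)/30.44, plus 3 or 12.
- w = 0: 5.5 and 14.5 months
- w = 8: 7.4 and 16.4 months
- w = 12: 8.3 and 17.3 months

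The early visit cannot occur on this count. The last visit is always at least 77/30.44 = 2.5 months past one year from inclusion.

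**5. The 12-month visit on the inclusion count**

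Months since session 12 = (365.25 − 7w − 77)/30.44: 9.5 at w = 0, 7.6 at w = 8 and 6.7 at w = 12. For these waits the long-term assessment follows the course on either count. The risk of measuring too early concerns the short-term assessment only.

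**The case against.** The best defence is that a coherent schedule lies behind the text. Twelve weekly sessions take roughly three months, so baseline, 3 months (end of course) and 12 months fits the abstract and the one-year follow-up, with post-intervention used as a loose column label. Table 2, and a work plan section that the article mentions, may set this out. This is plausible. But Study design and the evaluator item say something else in plain words, and a timeline figure cannot make those sentences agree with the inclusion sentence.

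The defence does limit what can be concluded. Several stronger readings are tempting, and the documents do not support them.

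- **That the 3-month BDI-II will be taken before the course ends.** This needs the inclusion sentence to govern, inclusion (undefined) to mean individual consent or baseline, and a wait of more than about two weeks. The article gives no fill time.
- **That one week's delay is enough.** Counting the course as twelve full weeks (84 days) leaves about 7 days of slack, but session 12 falls 77 days after session 1, so the slack is about 14.
- **That a power loss can be quoted.** That would need an assumed exposure and an assumed proportional effect. The remission rates behind the sample size (40% v 26%) are for 9 months, not the short-term visit. With last observation carried forward, the planned analysis set is also nearer 252 than 189 per arm.
- **That the arms will be seen at different times.** Patients in a centre are randomised together and evaluators are blinded, so the group's calendar is a natural anchor for its controls. The fault is only that no anchor is stated.
- **That the baseline BDI-II will be out of date and must be repeated.** The article does not say how old it would be at randomisation.

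**Conclusion.** The contradiction is certain: the primary outcome is timed from the intervention in some places and from inclusion in another, and the two differ by at least about 2.5 months for the same patient. It needs correcting because it leaves open when the main result is measured.

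The consequences are conditional. If inclusion means individual consent or baseline, a wait of more than about 14 days puts the 3-month BDI-II before session 12. With centres filling evenly over 4 to 12 weeks (an assumption), that would affect about half to four-fifths of a centre's patients. It can dilute the short-term effect, by an amount the documents do not allow anyone to state. If the intervention is the starting point, the last visit comes about 14.5 months or more after inclusion, which does not match the 1-year economic comparison, and controls have no stated reference date. Separately, the intention-to-treat set rests on events that can precede randomisation.

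**What to change.** Reconcile the abstract, Study design, both paragraphs of Recruitment process and Table 3 to one day zero for both arms: the centre's randomisation date.

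- Place the first follow-up after session 12 of that centre's group, on the same dates for its control patients.
- Place the last follow-up at 12 months from randomisation, so that it matches the 1-year QALY and cost comparison.
- Define the intention-to-treat set as all randomised patients.
- Check that Table 2 shows the same schedule.

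The cost is wording and visit scheduling, with no added visits or procedures. One consequence should be stated openly: the last visit then falls at most about 9.5 months after session 12, so the one-year result should be described as one year from randomisation, not one year after the course.

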**Table 2 Tab2:**
[figure not shown]
Data collection and intervention programme timeline

*Abbreviations*: *PHC* primary healthcare center, *IG* intervention group, *mo* months

Ethical approval has been provided by the Comitè Ètic d’Investigació (CEI), Fundació Institut Universitari per a la recerca a l’Atenció Primària de Salut Jordi Gol i Gurina (IDIAPJGol), Barcelona, Spain.

### Measures

The selected variables and instruments, as well as the evaluation program timeline, are detailed in Table 3. Data will be imported using an online survey tool and include:

**Table 3 Tab3:** Outcome measures

Outcome measures	Timeline		
	Pre-intervention	Post-intervention	
		3 mo	12 mo
1. Socio-demographic variables			
Sex, age, marital status, educational level, employment status, reference PHC	X		
2. Diagnostic variables			
Diagnosis depression: MINI	X		
Diagnosis chronic physical illness: ICD-10	X		
Suicide risk: MINI	X		
Cognitive impairment: Pfeiffer questionnaire	X		
3. Clinical variables			
Depressive symptoms: BDI- II questionnaire	X	X	X
Anxiety symptoms: HARS questionnaire	X	X	X
Quality of life: EQ-5D-5 L questionnaire	X	X	X
Pharmacotherapy	X	X	X
Therapeutic compliance: Morinsky-Green test	X	X	X
Feasibility of the intervention	X	X	
4. Blood test and Physical parameters			
Type 2 diabetes mellitus: Analytical HBA1C	X		X
COPD: FEV1 and Medical Research Coincil (mMRC)	X		X
Asthma: Spirometry and Peak flow	X		X
Ischemic heart disease: Analytical cholesterol LDL and Blood pressure	X		X
5. Costs variables			
Pharmacological Treatment	X	X	X
Utilization of services: PHC and hospital	X	X	X
Other comorbidities	X		X
Costs derived from the intervention	X	X	X

*Abbreviations*: *mo* months, *BDI-II* Beck Depression Inventory secondary edition, *COPD* Chronic obstructive pulmonary disease, *EQ* EuroQuol, *FEV1* Forced expiratory volume, *HARS* Hamilton Anxiety Rating Scale, *HBA1C* Hemoglobin A1C test, *ICS-10* International classification of diseases-10th revision, *MINI* Mini international neuropsychiatric interview, *PHC* Primary Healthcare Centers

Diagnostic variables*Diagnosis of depression* according to the MINI interview [27, 28].*Physical diseases* (code CIE-10). Diagnosis of diabetes mellitus (E11-E14 and sub-groups), COPD (J43-J44 and sub-groups), asthma (J45), and/or ischemic cardiopathy (I20-I25 and sub-groups) as registered in the patients’ medical records and confirmed by their family doctor [29].*Risk of suicide* evaluated by the MINI interview [27, 28].*Pfeiffer Scale* to detect cognitive impairment [30, 31]. This is a hetero-administered questionnaire made up of 10 items and scored from 0 to 10 (errors). From 5 onwards an individual is considered to present moderate/severe cognitive decline.

Socio-demographic variables:

Sex, age, civil status, educational level (without studies / incomplete primary ones / completed primary ones / secondary ones / higher education), employment status (employed / housewife / unemployed / disabled / retired). Assigned PHC: rural (doctor’s surgery) / semi-urban (PHC with a population < 15,000 inhabitants) / urban (PHC with a population ≥ 15,000 inhabitants).

Primary outcomes*Clinical remission and/or response of depression* at short and long-term (one year follow-up) of the intervention following Riedel et al. [32]: clinical remission considered as a reduction in the rating < 13 of the BDI-II; response to the intervention as a decrease of at least 50% in the initial evaluation of depressive symptoms according to the BDI-II.

Secondary outcomes

*Improvement in the control of the chronic pathology* at 12 months follow-up:
Diabetes mellitus: controlled with glycosylated hemoglobin, HBA1C (%) [33, 34].COPD: lung function measured by post bronchodilator expiratory volume (FEV1). Dyspnea evaluated by the modified score of the Medical Research Council (mMRC), at 5 points [35, 36]Asthma: lung function measured by post bronchodilator expiratory volume (FEV1). Determination of peak expiratory flow (PEF) [37].Ischemic cardiopathy: measurement of levels of low-density lipoprotein cholesterol and blood pressure [38].
2.*Adherence to medication* is assessed by the *Morinsky-Green* test [39] and the comparison between containers collected in the pharmacy and those prescribed. It will be performed for all the prescribed medication for both groups.3.*Quality of life* as measured with the *EuroQol (EQ-5D-5 L)* questionnaire. (Original: EuroQol Group 1996. Spanish adaptation: Badia et al. 1999) [40, 41].4.*Utilization of healthcare services* during the study period. This includes: number of hospital admissions (emergency room and ward) due to complications arising from diabetes, COPD, and ischemic cardiopathy (yes/no), and psychiatric pathology (yes/no); mental health referrals (yes/no) and number; and consultations with the family doctor/nurse (yes/no) and number.5.*Variables resulting from the intervention with respect to its feasibility.* A questionnaire with 10 items and a Likert scale of 4 categories regarding satisfaction is administered to the patients on completing the intervention. Adherence is assessed through the number of sessions each IG patient attends. An adherence variable is calculated for the intervention: ≥75% attendance or less.

Confounding variables and effect modifiers*Pharmacological treatment.* The defined daily dose for each active ingredient is established during the follow-up period taking into account the number of days, the dosage, and the route of administration. The registered active ingredients belong to the following groups: antidepressants, anxiolytics, antidiabetics (oral, insulin), bronchodilators (selective agonists of Beta2 - adrenergic, anticholinergic), anti-inflammatories: corticosteroids, antihypertensives, and dyslipidemics.*Other associated comorbidities:* cardiac insufficiency, atrial fibrillation, cardiovascular disease, peripheral vascular disease, other chronic diseases.Participation in *other mental health therapies* given by psychologists and psychiatrists.*Anxiety* evaluated with the HARS-Hamilton Anxiety Rating Scale [42].*History of previous depressive episodes* (yes/no).

Cost variables

Expenses included in the cost-effectiveness analysis:*Use of primary care services*: consultation fees according to professional status and level of care.*Use of hospital services*: hospitalization and emergency room consultations.*Cost of psychotropic medication consumed during the study*: anxiolytics and antidepressants according to the current catalogue from the Pharmacist Association.*Derived costs*: training and supervision of the nurses responsible for leading the sessions, their working hours spent with the groups, and expenses related to material used in the sessions and given out to the participants. In order to calculate the cost of the resources 2016 Oblikue rates are employed [43].

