**Main measurements:**

Clinical remission of depression and/or response to intervention (BDI-II).

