### Sample size

A power analysis will be conducted to determine the appropriate sample size. A previous study of psychoeducation programs [18] reported a remission rate at 9 months follow-up of 40% in the IG and 26% in the CG. Assuming a 5 and 20% alpha and beta risk, respectively, 189 patients are required for each group. Due to a number of reasons, an approximately 25% dropout rate is expected, consequently, 252 participants per group need to be recruited (total *n* = 504). In addition, 25 PHC are required each with a mean of 20 patients (IG *n* = 10, CG *n* = 10).

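### Remission and/or response is primary at two visits with no deciding result named, while the sample size covers a single remission test

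*Protocol article*

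**What the plan says.** In the protocol article, Measures, under a plural heading for primary outcomes, the outcome is "Clinical remission and/or response of depression", assessed "at short and long-term (one year follow-up) of the intervention". Each component has its own definition:

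- Remission: "clinical remission considered as a reduction in the rating < 13 of the BDI-II".
- Response: "response to the intervention as a decrease of at least 50% in the initial evaluation of depressive symptoms according to the BDI-II".

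The Recruitment process section and Table 3 place the BDI-II at baseline, 3 months and 12 months.

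The link between the two components changes from section to section. The Abstract's main measurement is "Clinical remission of depression and/or response to intervention (BDI-II", and its background paragraph uses a slash. The primary hypothesis at the end of the Background joins them with a plain and. So does Statistical analysis, where "logistic regression is employed in which the dependent variable is dichotomous (rate of remission and response". That sentence names no visit. The section then adds: "Raw and adjusted odds ratio (OR) are calculated according to age, sex, pharmacologic treatment, and comorbidity".

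The Sample size section rests on an earlier study that "reported a remission rate at 9 months follow-up of 40% in the IG and 26% in the CG". It takes 5% alpha and 20% beta, arrives at 189 per group, and raises this to 252 per group for 25% dropout.

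**The concern.** Either component, one composite of the two, or both jointly are different endpoints, and each is measured at two visits. The article does not say which result decides whether the intervention worked. A trial in which, say, response at 3 months is significant and remission at 12 months is not could be reported as meeting its primary aim, and a reader holding this document could not dispute it. The chance of a false claim would then exceed 5%, and the stated 80% power would belong to only one of the possible tests.

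The article states a multiple primary outcome and sizes the trial for a single one. That is a mismatch between two things it fixes, rather than a detail deferred to an analysis plan.

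**Working it through.** **1. Reproducing the stated sample size.** Inputs from Sample size: p1 = 0.40, p2 = 0.26, d = 0.14, mean 0.33, alpha 5%, power 80%. Two-sided testing is assumed because sidedness is not stated.

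n = [1.960·√(2·0.33·0.67) + 0.842·√(0.40·0.60 + 0.26·0.74)]² / 0.14² = 175.9, i.e. 176.

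With continuity correction: (175.9/4)·[1 + √(1 + 4/(175.9·0.14))]² = 189.9, i.e. 190 against the stated 189. Dropout: 189/(1 − 0.25) = 252, exact. One-sided versions give 139 or 153. The stated number therefore fits one two-sided test of remission at the full 5%, with nothing set aside for a second test.

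**2. False-positive rate if any significant primary result counts.** For k independent tests it is 1 − 0.95^k: 9.75% for k = 2 and 18.5% for k = 4. These tests are correlated, so the rate is lower. With equally correlated normal test statistics:

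| Correlation | 2 tests | 4 tests |
|---|---|---|
| 0.5 | 9.1% | 15.6% |
| 0.7 | 8.4% | 13.1% |
| 0.9 | 7.0% | 9.4% |

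**3. Null simulation on the BDI-II scale.** Assumptions, none of them given in the article: 189 per arm, entry scores uniform over 13–28, follow-up mean 0.85 times the entry score, residual SD 8, residual correlation between visits of 0.3, 0.5 or 0.7, and 20,000 trials per setting. Each single test rejected in 4.8–5.2% of trials. The chance of at least one p < 0.05 was:

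| Tests | Result |
|---|---|
| Remission at both visits | 8.8–9.5% |
| Either/or composite at both visits | 8.9–9.6% |
| Remission and response, each at both visits | 14.3–15.1% |

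A run closer to the stated design used 252 per arm, 25% dropout, last observation carried forward, and entry scores from N(22, 7) limited to 13–28. It gave 8.5%, 8.7% and 13.4%. Over all settings tried, the ranges are about 8–10% for two tests and 12–15% for four.

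**4. Power if the 5% is shared equally.** With 189 per arm, the continuity correction and critical value z:

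Φ{[0.14 − 1/189 − z·√(0.4422/189)] / √(0.4324/189)}

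- One test, z = 1.960: 79.8%.
- Two tests, alpha 0.025 each, z = 2.241: 70.9%.
- Four tests, alpha 0.0125 each, z = 2.498: 61.4%.

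**The case against.** The best defence is that the plan has one composite. Statistical analysis speaks of a single dichotomous variable, so and/or may simply mean remission or response. The two definitions also overlap heavily: for any entry score from 13 to 25, halving it gives 12 or less, so every responder is already a remitter. Only patients entering at 26 or above can respond without remitting. In the simulation the composite rate was 29.7% against 29.1% for remission alone, so the sizing fits the composite closely. This stands, and it removes the 12–15% figure on that reading. It does not remove the second visit, so about 8–10% remains.

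It can also be said that the article never states that any one significant result is enough, and that testing order is often left to an analysis plan. The first half is true and is carried as an assumption. The second does not cover a primary outcome that the article itself defines at two visits and words in three ways.

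A sponsor may add that carrying values forward brings all 252 per arm into the analysis. Nominal power without continuity correction is then 86.7% for two tests and 80.3% for four. That assumes patients with carried-forward values still show 40% against 26%, and it leaves the false-positive rate untouched.

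A reader might infer something stronger: count remission, response and the composite at two visits as six tests, and add more for the raw and adjusted odds ratios. The documents do not support this. The composite and the separate components are alternative readings of one phrase, so adding them describes no stated plan. The raw and adjusted odds ratios address the same contrast in the same patients and are highly correlated. What is missing there is only which of the two decides.

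**Conclusion.** The point holds. The primary outcome is not reduced to one endpoint at one visit, and the sample size is for one remission test whose 9-month rates match no visit in this trial. The sample size arithmetic is sound for that one test.

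If any significant primary result counts as success, the false-positive rate is about 8–10% with one endpoint or the composite at two visits, and about 12–15% with remission and response each at two visits. These sizes depend on that inferred success rule, on two-sided 5% tests and on assumed BDI-II distributions. If the test statistics were correlated at 0.9, they would fall to 7.0% and 9.4%, still above 5%.

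**What to change.** Before outcome data are unblinded, name one primary endpoint at one visit, tested once with one named model, and say which odds ratio decides. Remission (BDI-II below 13) at 12 months is the natural choice, because the 189 per arm was computed for remission and the trial has a one-year follow-up. The article does not compel that visit, so the sponsor should state its choice. The time origin of the visit also needs stating, since Study design counts from the intervention and Recruitment process counts from inclusion.

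Make response and the 3-month results secondary in a fixed sequence. Use the same wording in the Abstract, objectives, Measures and Statistical analysis, and update the registration to match.

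If the sponsor prefers more than one primary test, it should state the alpha split and restate the power at 189 per arm, about 71% for two tests and 61% for four under an equal split. Restoring 80% by the same formula would take 228 evaluable and 304 recruited per arm for two tests (608 in all), or 265 and 354 for four (708 in all).

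The single-test route needs no extra patients or visits, and 189 evaluable with 252 recruited per arm stands. Its cost is that response and the short-term results lose primary status.
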